## Abstract

**Background:**

Rheumatoid arthritis (RA) is a chronic autoimmune condition that results in pain and disability. Patients with RA have a decreased functional ability and are forced into a sedentary lifestyle and as such, these patients often become predisposed to poor bone health. Patients with RA may also experience a decreased health related quality of life (HRQoL) due to their disease. Whole body vibration (WBV) is a form of exercise that stimulates bone loading through forced oscillation. WBV has also been shown to decrease pain and fatigue in other rheumatic diseases, as well as to increase muscle strength. This paper reports on the development of a semi randomised controlled clinical trial to assess the impact of a WBV intervention aiming to improve functional ability, attenuate bone loss, and improve habitual physical activity levels in patients with RA.

**Methods/Design:**

This study is a semi randomised, controlled trial consisting of a cohort of patients with established RA assigned to either a WBV group or a CON (control) group. Patients in the WBV group will undergo three months of twice weekly intermittent WBV sessions, while the CON group will receive standard care and continue with normal daily activities. All patients will be assessed at baseline, following the three month intervention, and six months post intervention. Main outcomes will be an improvement in functional ability as assessed by the HAQ. Secondary outcomes are attenuation of loss of bone mineral density (BMD) at the hip and changes in RA disease activity, HRQoL, habitual physical activity levels and body composition.

**Discussion:**

This study will provide important information regarding the effects of WBV on functional ability and BMD in patients with RA, as well as novel data regarding the potential changes in objective habitual physical activity patterns that may occur following the intervention. The sustainability of the intervention will also be assessed.

**Trial registration:**

PACTR201405000823418 (19/05/2014).

**Electronic supplementary material:**

The online version of this article (doi:10.1186/1471-2474-15-403) contains supplementary material, which is available to authorized users.

## Background

Rheumatoid Arthritis (RA) is the most common, chronic autoimmune disease. It results in joint swelling, tenderness and destruction of the synovial joints, pain, severe disability, and decreased functional ability [1]. RA occurs in 1% of people worldwide, with the prevalence being two times higher in women than in men [2].

The health assessment questionnaire (HAQ)- a disease specific measure of functional ability in RA, is a widely used outcome measures for RA [3]. A large qualitative study conducted in female patients with RA found that patients report pain and decreased functional ability as having the most widespread effect on their daily lives [4]. Inability to perform normal daily activities not only decreases health related quality of life (HRQoL), but also further perpetuates a sedentary lifestyle. HAQ scores have been shown to be improved in patients with RA who have participated in exercise interventions aimed at increasing their regular levels of physical activity [5].

Physical activity as a functional measure of HRQoL can be difficult to assess. Commonly used questionnaires and recall diaries are subjective [6] and rely on fluency in the English language. Accelerometers are thus growing in popularity as an objective way to measure physical activity, especially in healthy populations [7]. Accelerometers are small, unobtrusive and comfortable, and measure acceleration of the limb to which they are attached by detecting low frequency (0.5-3.2 Hz) gravitational forces (0.05-2.0 g) [7]. Acceleration is directly proportional to muscle forces generated, which is proportional to energy expenditure [8]. This theory along with an inbuilt algorithm allows for the conversion of acceleration into activity counts. These counts can be classified into thresholds, indicating light, moderate or heavy intensity levels [8]. Accelerometers are able to track intensity, duration and frequency of an activity without relying on patient recall [9]. Actical accelerometers in particular, can detect varying levels of activity, being able to detect lower level activities and movement in multiple planes [7] and may therefore be an ideal tool for measuring physical activity and sedentary behaviour in patients with RA, where most movement is functional and of a low frequency and intensity, and therefore unlikely to be reported accurately using self report measures. Indeed accelerometry has already been used to this effect in other rheumatic diseases [10]. Although there is a paucity of research which has objectively assessed physical activity levels in people with RA, our group, as well as Semanik et al. [11] have recently demonstrated that sedentary behaviour as assessed using accelerometery is indeed more prevalent in patients with RA when compared to their healthy counterparts [12].

Patients with RA have lower bone mineral density (BMD) at the hip, spine, and whole body than age matched controls [13]. Lower BMD and higher incidence of osteoporosis in patients with RA may be as a result of the presence of circulating inflammatory cytokines inherent to the disease, the decreased mobility of these patients, or due to certain medications taken to treat the disease such as corticosteroids. Osteoporosis in RA can be generalised or peri-articular in nature. Studies have shown that the majority of bone density loss in RA occurs in the first six months of disease [14]. Furthermore, patients with higher RA disease activity have been shown to exhibit a greater loss in BMD, as well as higher indices of bone metabolism compared to those with lower disease activity. Mobility and functional ability have been correlated with BMD; as have age, stature, and sex independently of RA disease [15, 16].

The skeleton transforms it’s mass and morphology according to individual activity levels and forces placed upon the bone [17]. Furthermore a minimum effective strain must be placed upon bone in order for remodeling to occur [18]. A sedentary individual does not place sufficient strain on the skeleton, and bones are thus remodeled in a direction that promotes bone loss. Patients with RA are therefore at increased risk of osteoporosis due to inflammatory processes inherent to their disease; as well as their sedentary lifestyle [19]. Bone mass in RA can be modified using treatments designed to increase bone mass; decrease RA disease activity; and by increasing physical activity or decreasing sedentary behavior sufficiently in order to increase bone loading and remodeling. Research has shown that exercises aimed at increasing or attenuating loss of BMD should be dynamic- comprised of short and vigorous bouts of high impact exercise incorporating rest periods [20], yet this type of exercise is usually not feasible in patients with a chronic, disabling pain condition such as RA.

Exercise interventions making use of light aerobic activity, strength training, and stretching, have produced varied results in cohorts of RA patients. Most studies show exercise improves physical fitness and muscle strength with either no change or improved disease activity outcomes [21], however these interventions have not specifically addressed the problem of low bone mass in these patients. Whole body vibration (WBV) is a potential novel exercise intervention for people with RA. WBV therapy is an exercise whereby a mechanical vibration platform produces energy via forced oscillation. The vibratory waves are then transferred to an individual via propagation through the feet, legs, trunk and finally, the head [22]. Although the exact mechanisms whereby WBV therapy increases BMD are unclear, it is likely that there are multiple mechanisms at play. WBV has been shown to activate fluid flow in the caniliculi and lacunae of bone matrix in rats [23], in a manner proportional to loading frequency. This fluid flow creates shear stress on the plasma membrane of osteocytes, bone lining cells, and osteoblasts, which therefore respond accordingly [20]. WBV thus activates mechanotransduction in bone and stimulates osteogenesis [23]. Furthermore, muscle forces have been shown to exert the greatest osteogenic stimulus on bone, and the generation of these forces through vibration stimulus is likely a contributor to the skeletal adaptations that occur [24]. Vibratory stimuli must sufficiently load bones in order to increase bone deposition.

WBV has been used to treat osteoporosis in otherwise healthy populations with low BMD [23], older individuals [25], postmenopausal women [26], athletes at risk of osteoporosis [27], as well as in other diseased populations [28] with mainly positive results including increased or attenuated loss of BMD, increases in muscle strength, improved proprioception and balance, and decreased pain and fatigue levels. Furthermore, WBV therapy has been shown to increase peripheral blood flow [29] as well as cardiovascular performance [30], and could therefore have an effect on cardiovascular health. Trans et al. [31], used WBV in patients with knee osteoarthritis and found 8 weeks of twice weekly vibration training to significantly improve knee strength in these patients, but did not assess BMD. Alentorn-Geli et al. [32] used a dynamic and static WBV protocol, twice weekly for 6 weeks in a group of female patients with fibromyalgia. Patients in this study were divided into a control group who underwent no therapy, an exercise group who underwent standard RA exercise therapy only, and a WBV group who underwent WBV training on top of the standard exercise therapy. The authors of this study found that the WBV protocol significantly improved fatigue scores, as well as pain scores in comparison to the exercise group and the control group, however no measures of BMD were taken. Other studies have shown WBV therapy to have no effect on BMD in healthy adults [33], or on fatigue or pain levels, balance, or strength [34].

WBV has not, to our knowledge, been used as an exercise intervention for RA, yet it may be a feasible means to increase functional ability in these patients. Since patients with RA are already at risk for developing osteoporosis, and are therefore at greater risk of fracture; WBV could also potentially be a means to attenuate the progressive loss of BMD observed in patients with RA, without the need for a vigorous exercise programme. Previous studies that have used WBV in other chronic inflammatory or pain conditions do not suggest that WBV would elicit any adverse effects in this population. With this background in mind, the aims of this study are primarily to determine the effects of a WBV programme on functional ability in patients with established RA in comparison to a control group of patients, as well as to determine any effects WBV therapy may have on BMD, disease activity, physical activity levels, HRQoL, or body composition in these patients.

## Methods

### Study design

A semi randomised, single blinded, controlled, two-group parallel design in accordance with the 2010 CONSORT guidelines will be used; with patients being allocated to either group in an alternating manner upon enrollment. Patients in the WBV group will begin a WBV therapy intervention programme for a three month period, while those in the CON group will continue to receive standard care for the three month period. All patients will be assessed at three time points, as shown in Figure 1.

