**Flow diagram of study design.**

### Participants

Fifty participants will be recruited from the Rheumatology Clinic at the Chris Hani Baragwanath Academic Hospital in Soweto, South Africa. Recruitment will include the outpatients attending the clinic at the quarterly check-up via a brief interview following dissemination of study information. Consenting patients will be included if they are older than 18 years, have been diagnosed with RA (according to the 1987 ACR criteria [35]) at least three years previously, are on stable drug therapy (prednisone <10 mg/day), and had been for at least three months previously. Patients will be excluded if they are HIV+, are using bisphosphonates or corticosteroids, have any co-morbidities that could potentially impact on physical activity levels, are using assistive walking devices, have previously had hip or knee joint replacement surgery, and if they are pregnant.

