### Intervention and control

All vibration training will be performed on standard power plates (DKN XG 5.0, DKN Technology, California, USA) under the supervision of the primary investigator. Vibration training will consist of 24 total sessions (performed twice weekly for 12 weeks); in intermittent bouts of 60 seconds on the plate and 30 seconds off the plate, repeated 10 times (this protocol was designed to stimulate greater osteogenic responses due to the constant stimulus to the mechanoreceptors [27]). Patients will be required to stand on the plates, barefoot and with knees slightly bent, holding firmly to the bars. Vibration plates will be set at a constant frequency of 30Hz and amplitude of 3 mm in order to maximize the osteogenic and muscle activation effects of the therapy [27]. The CON group will continue to receive standard care for the intervention period, and will be instructed to continue with their normal daily activities for the three month period.

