#### BMD

All patients will be assessed, for site specific areal BMD at the left hip, lumbar spine (L1-L4), and whole body using Dual X-Ray Absorbtiometry (DXA). T and Z scores will then be calculated according to reference values. All scans will be performed by the same qualified technician on the same machine (Hologic QDR 4500A, Hologic, Boston, USA). The machine is routinely calibrated, and a phantom spine will be scanned daily to determine coefficients of variation of the machine. The technician will be blinded as to the grouping of participants during the study. According to previous studies examining bone loss over time in age matched female patients with RA [38], and the effects of exercise interventions on this type of bone loss [39]; we expect a decrease of approximately 0.33% in hip BMD in the control group, and for this loss to at least be attenuated in the WBV group.

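### Allocation alternates in order of enrolment with no concealment described, so the next assignment is predictable to anyone who knows the last one and the comparison is open to selection bias

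*Protocol article*

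**What the plan says.** The abstract (Methods/Design) introduces the trial with the words "This study is a semi randomised, controlled trial consisting of a cohort of patients with established RA assigned to either a WBV group". The Study design section says "A semi randomised, single blinded, controlled, two-group parallel design in accordance with the 2010 CONSORT guidelines will be used", and the same sentence gives the mechanism: "with patients being allocated to either group in an alternating manner upon enrollment". The article describes no random sequence and no concealment of upcoming assignments.

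On enrolment, the Participants section says "Fifty participants will be recruited" from one hospital clinic. The route is "Recruitment will include the outpatients attending the clinic at the quarterly check-up via a brief interview following dissemination of study information". The person who conducts the interview is not identified. Most exclusions are matters of fact, such as HIV status, earlier joint replacement, walking aids and pregnancy. One needs judgement: patients are excluded if they "have any co-morbidities that could potentially impact on physical activity levels".

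Under Intervention and control, all vibration training takes place "under the supervision of the primary investigator". The blinding that the article specifies concerns outcome assessment. For the bone scans, "The technician will be blinded as to the grouping of participants during the study", and the Disease activity section makes a similar statement about the assessing physician. The Statistical analysis section plans an intention-to-treat analysis and unpaired t-tests on absolute HAQ and on change in HAQ, with no baseline adjustment named.

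**The concern.** A random, concealed sequence ensures that whoever decides on a patient's entry cannot know which group that patient will join. Alternation gives no such assurance. Once one assignment is known, so is the next, and then the order of approach, the encouragement given or the reading of a discretionary criterion can vary with the group that is due. This need not be deliberate.

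Every between-group comparison in the trial rests on this step. If patients with a better outlook or more motivation tended to enter the vibration group, which asks for 24 supervised sessions, a difference in the patient-completed HAQ could reflect who entered each group as well as what the treatment did. No later analysis reliably repairs that, because factors such as motivation are not measured.

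**Working it through.** **1. Predictability of the sequence.** The inputs are N = 50 (Participants) and strict alternation (Study design). Assignment k is the opposite of assignment k − 1 for k = 2 to 50.
- Determined by the previous assignment: 50 − 1 = 49, and 49/50 = 98%.
- If the starting group is also known: 50/50 = 100%.

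For comparison, 4,000 simulated sequences of 50 gave the share of assignments known with certainty to someone who sees all earlier ones and knows the block size: about 32% with blocks of 4, about 24% with blocks of 6, and about 4% with a single 25:25 random list. Concealment and randomly varying block sizes are meant to deny the recruiter even that knowledge.

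**2. Do the other safeguards act at enrolment?**
- Blinding of the scan technician and the assessing physician acts at outcome assessment, after allocation.
- Intention-to-treat analysis keeps patients in the group they were allocated to, so it also keeps any imbalance created at entry.
- Unadjusted t-tests do not correct for differences at entry. Comparing the groups at baseline can reveal measured imbalance but cannot rule out unmeasured imbalance.
- The change-score t-test does help in part. If selection only adds a constant δ to one group's HAQ at every visit, then (follow-up + δ) − (baseline + δ) = follow-up − baseline, and δ cancels. A difference in expected course or in motivation does not cancel.

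**3. Illustration of size for the absolute-score test.** The documents give no figure for the bias, so the shift δ is an assumption. Other inputs:
- n = 20 per group: 50 less the roughly 20% attrition under Potential obstacles leaves 40, or 20 per group.
- SD = 0.19, from the Sample size section. That section does not say whether it is the SD of a score or of a change, so an assumed 0.40 is shown as well.
- Two-sided 5% level, no true effect.

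The test statistic follows a noncentral t distribution with 2n − 2 = 38 degrees of freedom and noncentrality δ / (SD × √(2/n)). The critical value is 2.024. The denominator is 0.19 × √(2/20) = 0.0601, or 0.40 × √(2/20) = 0.1265.

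| Assumed shift δ (HAQ) | Noncentrality, SD 0.19 | Type I error, SD 0.19 | Noncentrality, SD 0.40 | Type I error, SD 0.40 |
|---|---|---|---|---|
| 0.02 | 0.33 | 6.2% | 0.16 | 5.3% |
| 0.05 | 0.83 | 12.8% | 0.40 | 6.7% |
| 0.10 | 1.66 | 36.8% | 0.79 | 12.0% |

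With all 25 per group and SD 0.19, the three error rates are 6.5%, 14.9% and 44.6%. For scale, the Sample size section uses a difference of 0.22 between groups.

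**The case against.** The strongest reply is that the article shows only that selection is possible. It does not say who recruits, who keeps the sequence, or whether that person sees earlier assignments. It is open about its method: it says semi-randomised and states the alternation in the same sentence. Most eligibility criteria are objective. The plan also includes a change-score analysis, in which a stable HAQ difference at entry disappears.

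Much of this stands, and it rules out some stronger readings that a reader might infer:
- That the recruiter always knows the next group. The text supports only that the group is predictable to anyone who knows the previous assignment, and the first is predictable only if the starting group is known.
- That the sequence could not possibly be concealed. The text supports only that no concealment is described and that the sequence is easily inferred.
- That the t-tests are helpless against any imbalance. The change-score test removes a constant one.
- That the false-positive rate will be 37%. That is one corner of an assumed range. It depends on an invented shift of 0.10 and on reading 0.19 as the SD of an absolute score.
- That readers are misled about the mechanism. They are not, because it is disclosed.

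None of this makes alternation random or protects enrolment. It is also not a detail left to a fuller document: the article states the method outright, and no other document could make it random without contradicting that sentence.

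**Conclusion.** The concern holds as a weakness in the stated design. Allocation is deterministic, no concealment is described, and 49 of 50 assignments (all 50 if the starting group is known) can be predicted from the one before. Interview recruitment at one clinic, one discretionary exclusion and an investigator who sees who attends for vibration training make it plausible that enrolling staff could know earlier assignments, though the article does not say that they do.

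Whether bias would occur, and how much, is unknown. Across assumed shifts of 0.02 to 0.10 HAQ points and SDs of 0.19 and 0.40, the type I error of the absolute-score test with 20 per group runs from about 5% to about 37%. These figures do not apply to the change-score test, where the remaining risk is a difference in prognosis or motivation that cannot be quantified from the documents. The case for changing the method rests on predictability. It affects every between-group comparison and has to be dealt with at enrolment.

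**What to change.** Replace alternation with a computer-generated 1:1 sequence in randomly varying permuted blocks. Have someone who takes no part in recruiting prepare sequentially numbered, sealed, opaque envelopes, and open each one only after consent, confirmation of eligibility and baseline assessment. Then remove the references to alternation and semi-randomisation and describe the trial as randomised.

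If patients have already been allocated by alternation, describe that part of the trial as non-randomised (quasi-randomised) and compare follow-up HAQ between groups with adjustment for baseline HAQ. The adjustment deals with measured HAQ imbalance only, so the limitation should be stated alongside the result.

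The cost is one list, a set of envelopes and a short amendment. Treatment, visits and outcomes stay as they are. The small downside is that group sizes may differ by a few patients.

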**Figure 1 Fig1:**
[figure not shown]
**Flow diagram of study design.**

### Participants

Fifty participants will be recruited from the Rheumatology Clinic at the Chris Hani Baragwanath Academic Hospital in Soweto, South Africa. Recruitment will include the outpatients attending the clinic at the quarterly check-up via a brief interview following dissemination of study information. Consenting patients will be included if they are older than 18 years, have been diagnosed with RA (according to the 1987 ACR criteria [35]) at least three years previously, are on stable drug therapy (prednisone <10 mg/day), and had been for at least three months previously. Patients will be excluded if they are HIV+, are using bisphosphonates or corticosteroids, have any co-morbidities that could potentially impact on physical activity levels, are using assistive walking devices, have previously had hip or knee joint replacement surgery, and if they are pregnant.

